## Abstract

**Simple Summary:**

Radiation-induced heart disease represents a spectrum of early and late effects. It is a significant concern for cancer survivors who receive thoracic radiation therapy, as it is the most common nonmalignant cause of death in this population. Subclinical cardiac damage can be detected at an early stage after irradiation and may possibly be used to predict late cardiac complications. Modern radiotherapy techniques, such as deep inspiration breath-hold radiotherapy or intensity-modulated radiation therapy, can reduce the heart dose and probably do not cause alterations in myocardial perfusion. This paper describes the study protocol we will use to evaluate perfusion defects after left-sided breast radiotherapy using myocardial perfusion single-photon computed tomography.

**Abstract:**

Breast radiotherapy can lead to radiation-induced cardiac disease, particularly in left breast cancers. Recent studies have shown that subclinical cardiac lesions, such as myocardial perfusion deficits, may occur early after radiotherapy. The primary method for irradiating breast cancer, known as opposite tangential field radiotherapy, can cause the anterior interventricular coronary artery to receive a high dose of radiation during left breast irradiation. To explore alternative approaches that could reduce the risk of myocardial perfusion defects in patients with left breast cancer, we plan to conduct a prospective single-center study using a combination of deep inspiration breath hold radiotherapy and intensity modulated radiation therapy. The study will use stress and, if necessary, resting myocardial scintigraphy to assess myocardial perfusion. The trial aims to show that reducing the cardiac dose with these techniques can prevent the appearance of early (3-month) and medium-term (6- and 12-month) perfusion disorders.

In patients with left-sided breast cancer, perfusion abnormalities are more commonly observed, indicating that the incidence of these defects is concentrated in the radiotherapy field and is linked to the degree of cardiac exposure [13,14,15]. In a study of 114 patients who received breast cancer irradiation, volume-dependent perfusion defects were detected in approximately 40% of patients within two years after irradiation. The occurrence of new defects was found to be approximately 10% to 20% in patients with less than 5% of their left ventricle included within the irradiation fields and 50% to 60% in those with greater than 5% of their left ventricle included (*p* = 0.33 and *p* < 0.001) [5].

Breast cancer irradiation is mainly achieved by a tangentially opposed field approach. Considering cardiac anatomy, when treating a left breast, it would be expected to have a high dose to the left anterior descending coronary artery (LADA) but not to the left circumflex and right coronary arteries [14,16]. The distribution of the dose to the heart is heterogeneous [17], and cardiac tissues are differently radiosensitive [18,19]. Therefore, MHD may not be the most relevant dose parameter to assess cardiac exposure [20].

In the era of modern radiotherapy techniques, cardiac substructures could be delineated to optimize heart dosimetry and protect patients from cardiac complications [21]. The use of reference atlases and autosegmentation software relevant to these substructures would save time, quality, and reproducibility in delineation and consequently in dose calculation [22,23].

The correlation between perfusion defects and radiation dose to the myocardium implies that strategies aimed at reducing the radiation dose have the potential to mitigate myocardial damage. The distribution of the radiation dose to the heart is contingent on several factors, including the radiation technique utilized, the irradiated volumes, and the location of the radiation field [24,25]. A variety of radiotherapy techniques are being used to spare the heart [26] by limiting the dose to the heart (intensity-modulated radiotherapy (IMRT), proton therapy) [27], by maneuvers to increase the distance from the heart to the target volume (deep inspiration breath-hold (DIBH), prone position) [28], or by changing the target volume and not including all the breast glandular tissue (partial breast irradiation) [29]. However, since RIHD appears clinically most often many years after irradiation, the clinical impact of these techniques remains uncertain.

The DIBH technique can effectively displace the heart posteriorly, medially, and inferiorly away from the breast and the deep border of the tangential fields. Some investigations have recently been performed to aid in the prediction of major beneficiaries of the DIBH technique using this beam arrangement [30,31], so that non-beneficiaries may be candidates for alternative RT techniques such as IMRT [32]. There is a clear correlation between the incidental radiation of the heart in left breast irradiation and the detection of early postradiotherapy perfusion defects, which highlights the importance of implementing heart sparing techniques. Studies suggest that DIBH may be beneficial in preserving cardiac perfusion, particularly with low cardiac doses of less than 5 Gy at 6 months and 1 year post-radiation therapy [33,34].

Advanced radiotherapy techniques, such as IMRT and VMAT, modify the distribution of doses to the heart by increasing low doses [35,36]. Biophysical models for normal tissue complications suggest that the relationship between radiation dose and heart complications follows a sigmoidal dose-response curve in this case [36], rather than a linear curve. Therefore, the risk of heart complications, which was estimated at 7.4% per Gy by Darby et al. [2], may be overestimated when smaller, more homogeneous doses are used.

This single-institution prospective study will assess the utility of DIBH utilizing a controlled surface monitoring technique (AlignRT, Vision RT Ltd., London, UK) and IMRT as a means of preventing cardiac perfusion defects as determined by cardiac gated-SPECT in patients receiving irradiation for left-sided breast cancer.

## 2. Materials and Methods

### 2.1. Study Setting

This interventional, nonrandomized, monocentric, descriptive, and prospective pilot study is being led by the University Radiotherapy Department of the Strasbourg-Europe Cancerology Institute (ICANS).

This study was approved by the Ethics Committee of Ouest VI in August 2022 and registered on clinicaltrials.gov in July 2022 (NCT05454553).

### 2.2. Participants

For a full overview of all inclusion and exclusion criteria, see Table 1.

### 2.3. Practical Conduct of the Study

#### 2.3.1. Screening Procedures and Baseline Evaluation

Eligible patients will receive detailed information about the study, including its characteristics, consequences, and constraints, through a patient information sheet and consent form, as well as through an oral explanation by the investigator. Patients who agree to participate in the study will be required to sign an informed consent form. Before initiating radiotherapy, the patients will undergo various examinations, including a chest CT scan in the treatment position to aid in 3D treatment planning and dose calculation, a chest CT angiography to identify cardiac substructures, and baseline cardiac gated-SPECT imaging.

#### 2.3.2. Treatment Phase—Radiotherapy

During the treatment phase of this study, patients will receive a standard course of breast radiotherapy administered in our department. However, there will be a difference in the treatment planning process as cardiac substructures will be delineated on simulation CT scans with the help of chest CT angiography on the Varian Eclipse treatment planning system (Varian Medical Systems), according to Feng’s atlas [22], to ensure homogeneity and reproducibility of the cardiac segmentation process. Delineated cardiac substructures will be: left atrium, left ventricle, right atrium, right ventricle, left main coronary artery, LADA, left circumflex artery, right coronary artery, pulmonary artery, superior vena cava, aortic valve, pulmonic valve, mitral valve, tricuspid valve, atrioventricular node, pericardium, ascending and descending aorta. Cardiac substructure delineation will be validated by an experienced senior radiation oncologist. Target volumes, irradiation doses, and orientation to the radiotherapy treatment machine will depend on the clinical situation, as in daily clinical practice. Dose constraints for organs at risk follow the RECORAD 2022 recommendations [37]. Planned target volumes are defined according to ESTRO guidelines [38]. Target volume coverage is: PTV = V_95%_ ≥ 95%, D_2%_ ≤ 107%, and D_max_ ≤ 110%.

#### 2.3.3. Follow-Up Phase

The follow-up will consist of cardiac gated-SPECT at 3 months, 6 months, and 12 months after the end of radiotherapy, in addition to the usual follow-up.

Before these examinations, a consultation with a nuclear medicine physician will be carried out, which will allow the collection of clinical data, including details of eventual side effects.

If a reversible perfusion defect is detected during the follow-up period, the patient will be referred to a cardiologist for exploratory coronary angiography and, if necessary, transcutaneous angioplasty.

### 2.4. Practical Implementation of Cardiac SPECT

Cardiac SPECT will be obtained using a dedicated CZT camera (D-SPECT, Spectrum Dynamics Medical, Caesarea, Israel). According to the study protocol, patients will be scheduled to undergo cardiac SPECT before and at 3, 6, and 12 months post-irradiation. Stress electrocardiogram (ECG)-gated SPECT will be performed after infusion of 3 MBq/kg 99mTc-tetrofosmin (Myoview^®^, General Electric Healthcare, Chicago, IL, USA) at peak pharmacological stress with regadenoson (single dosage: 400 µg; Rapiscan^®^, GE Healthcare, Chicago, IL, USA). Intake of xanthic bases such as caffeine will be discontinued 24 h before cardiac SPECT. Rest ECG-gated SPECT will be performed on the same day, 4 h after stress ECG-gated SPECT, with administration of 8 MBq/kg 99mTc-tetrofosmin only if stress ECG-gated SPECT shows abnormalities.

#### 2.4.1. Cardiac SPECT Settings

The gamma camera will be configured to use a 140 keV photopeak with a 10% energy window. The acquisition time will be determined by a precount value of one hundred six counts originating from the left ventricle. The images will be reconstructed with Spectrum Dynamics software, without attenuation correction, and gated into 16 frames per cardiac cycle.

Cardiac SPECT images will provide objective quantitative data on regional myocardial perfusion, regional wall motion, and ejection fraction. The quantitative analysis will be performed using Cedars-Sinai software (New York, NY, USA) for quantitative gated SPECT (QGS)/quantitative perfusion SPECT (QPS).

#### 2.4.2. Use of Regadenoson (RAPISCAN^®^)

The quality of the cardiac SPECT results is closely tied to the quality of the stress test that is performed. The stress test can be conducted through physical exercise, such as running on a treadmill or pedaling on a bicycle. To ensure that the test is satisfactory, the patient must achieve an appropriate heart rate level of at least 85% of their maximum theoretical rate during the physical exercise stress test. However, depending on their clinical history, up to 40% to 50% of patients may not be able to reach this heart rate threshold. If a physical stress test is inadequate, not recommended, or unfeasible for the patient, administration of a pharmacological stress agent through intravenous injection can be used to induce myocardial perfusion abnormalities.

To have a secure and reproducible protocol for patients, a myocardial stress scan will be performed with regadenoson, a pharmacological stress agent for radionuclide myocardial perfusion imaging.

Regadenoson causes a rapid increase in intravascular adenosine. Less than 60 s are needed to administer regadenoson (400 µg) and 99mTc-tetrofosmin. As a result, it is expected that the heart rate will increase while the blood pressure will decrease after the injection. Patients are advised to maintain a seated or lying position and should be closely monitored at regular intervals until ECG parameters, heart rate, and blood pressure have returned to their pre-injection levels.

The most reported adverse events following administration of regadenoson as a stress agent were dyspnea (28%), headaches (26%), rash (16%), and chest discomfort (13%), which typically occurred within 30 min. Overall, regadenoson was found to be well tolerated, with an incidence of serious adverse events of 1% [39,40]. Aminophylline may be used to attenuate severe and/or persistent adverse reactions to regadenoson. Due to the rupture issues that are currently encountered with regadenoson, two other molecules should be chosen for use in patients undergoing stress ECG-gated SPECT for the purposes of this study, namely, dipyridamole or dobutamine, according to the patient’s comorbidities. In the absence of rupture, administration of regadenoson will be preferred.

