#### 2.7.2. Qualitative Scoring of Changes on Cardiac SPECT

Postradiotherapy cardiac SPECT will be compared to baseline to assess changes in cardiac perfusion. Increases in SSS or SRS ≥ 3 points in one segment or ≥ 2 points in at least two segments between post- and pre-RT scans will be considered clinically significant.

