### 2.8. Statistical Analysis

#### 2.8.1. Sample Size

The estimation of the anticipated incidence of perfusion defects is approximately 17%. The two radiotherapy techniques evaluated (DBIH and IMRT) reduce heart exposure to irradiation. The objective of this dose reduction is to reduce the incidence of perfusion defects to 0%. Assuming an α of 0.05 and 80% power, and since two irradiation techniques are evaluated, the study should include at least 58 subjects to ensure adequate power and compensation for possible loss of patients during the protocol (Rosner B. Fundamentals of Biostatistics, 7th ed., Boston, MA: Brooks/Cole).

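### Section 2.4.2 picks the stress agent by supply on the scan date, not by the patient's baseline agent, so a change in SSS may partly reflect a change of drug

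*Protocol article*

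**What the plan says.** Section 2.4 schedules a stress scan before radiotherapy and at 3, 6 and 12 months after it, with regadenoson as the stress agent. Section 2.4.2 gives the reason for that choice: "To have a secure and reproducible protocol for patients, a myocardial stress scan will be performed with regadenoson". The same section opens with the remark that "The quality of the cardiac SPECT results is closely tied to the quality of the stress test that is performed".

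It then reports a supply problem in the present tense ("Due to the rupture issues that are currently encountered with regadenoson", where rupture means a stock shortage) and provides for it: "two other molecules should be chosen for use in patients undergoing stress ECG-gated SPECT for the purposes of this study, namely, dipyridamole or dobutamine". The choice between the two substitutes depends on comorbidities. The closing rule is "In the absence of rupture, administration of regadenoson will be preferred". Nothing in the section refers to the agent used at the patient's earlier scans.

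Sections 2.7.2 and 2.8.2 define the event as an increase in SSS or SRS of at least "3 points in one segment or ≥ 2 points in at least two segments between post- and pre-RT scans". Section 2.1 describes an "interventional, nonrandomized, monocentric, descriptive, and prospective pilot study". Section 2.8.1 anticipates an incidence of about 17% and states the aim: "The objective of this dose reduction is to reduce the incidence of perfusion defects to 0" per cent.

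**The concern.** A within-patient change can be read as a radiation effect only if the two scans were made under comparable conditions. Under this rule the agent depends on supply on the day of the scan. Four scans spread over about a year, begun during a shortage, make a change of supply between baseline and follow-up foreseeable. A patient first scanned on dipyridamole or dobutamine is steered to regadenoson later. A patient first scanned on regadenoson may be moved to a substitute in a new shortage.

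In either case the SSS difference compares two drugs as well as two time points. An agent effect could create an event or hide one. There is no unirradiated or conventionally treated group in which it would show. The stress result also decides whether a rest scan is done (section 2.4), and a reversible defect leads to referral for coronary angiography (section 2.3.3), so a false defect would have consequences for the patient as well.

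The conclusion at stake is the strong one. Section 4 would take a defect-free result as support for making both techniques reference treatments and for probably dropping specific cardiac monitoring afterwards.

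**Working it through.** No figure in the article is in dispute. The check has a textual part and an illustration of size.

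**Text.** Section 2.4.2 fixes the agent by supply and, within the substitutes, by comorbidity. Sections 2.7.2 and 2.8.2 fix the comparison as post- against pre-radiotherapy in the same patient. No sentence links the two. Table 1 excludes patients with a contraindication to regadenoson, so changes of agent would come mainly from supply.

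**Inputs from the article.** N = 58, anticipated incidence 17%, target 0% (section 2.8.1).

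**Inputs assumed.** m is the number of patients with a follow-up scan on a different agent from baseline: 0, 6, 12 or 29, that is 0%, 10%, 20% or 50% of 58. f is the probability that such a patient gains a false event: 0% to 5%. True incidence is taken as zero and patients as independent.

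**Chance of at least one false event**, 1 − (1 − f)^m:

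| m | f | Result |
|---|---|---|
| any | 0 | 0 |
| 6 | 0.02 | 1 − 0.98^6 = 0.114 |
| 12 | 0.02 | 1 − 0.98^12 = 0.215 |
| 12 | 0.05 | 1 − 0.95^12 = 0.460 |
| 29 | 0.02 | 1 − 0.98^29 = 0.443 |
| 29 | 0.05 | 1 − 0.95^29 = 0.774 |

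**Effect on the pooled comparison with 17%.** Exact (Clopper–Pearson) two-sided 95% upper limits:

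- 0/58: 1 − 0.025^(1/58) = 6.2%
- 1/58: 9.2%
- 4/58: 16.7%
- 5/58: 19.0%

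Five events are therefore needed before pooled data stop excluding 17%. The binomial probability of five or more false events is 0.0002 for m = 12, f = 0.05, and 0.0136 for m = 29, f = 0.05.

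**Same-agent subset with no events**, upper limit 1 − 0.025^(1/n):

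- 0/52 (10% discordant): 6.8%
- 0/46 (20%): 7.7%
- 0/29 (50%): 11.9%
- 0/20: 16.8%
- 0/19: 17.7%

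Twenty is the smallest subset in which zero events exclude 17%.

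**The case against.** The strongest reply is that the article nowhere says the three agents give different scores in the same patient. The remarks on stress-test quality and reproducibility arise where section 2.4.2 explains why drug stress is used instead of exercise; they do not compare one drug with another. That reading is right, and those remarks do not show an agent effect. The concern needs less: unmatched stress conditions may affect a within-patient change, and the rule does nothing to match them.

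Second, the event is coarse. From a normal segment it takes a new severe defect, or moderate defects in two segments, scored by a blinded reader with software support (section 2.7.1). SRS comes from rest scans made without a stress agent. This stands as a reason to expect few false events, but it does not exclude them.

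Third, the rates are assumed, and the 77% needs half the patients to change agent. This also stands: the range shows what could follow and does not estimate what will.

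Fourth, the article has no rule that one event fails the study, and ordinary reading variability could also produce one. True, but supply-driven switching is a source of error that the plan itself introduces and can largely avoid.

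Finally, recording the agent and running a sensitivity analysis may already be covered in the full protocol or SAP, and their absence from an article is no fault. The criticism therefore rests on the stated rule alone. The word preferred does not forbid keeping the baseline agent, but it points the other way.

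**Conclusion.** The concern holds. The rule as written permits a different agent at follow-up and, when supply returns, favours one for patients whose baseline scan used a substitute. Its effect on the primary endpoint cannot be sized from the article: frequency, magnitude and direction are unknown, and the effect may be nil. Under the assumed ranges, the chance of at least one false event runs from 0% to 77%, while the chance of enough of them to upset the pooled comparison with 17% is at most 1.4%. What is exposed is the 0% objective and the defect-free conclusion, which a single created or masked event would change. This should be corrected because correction is cheap and the error would sit in the primary measurement; it does not invalidate the design. Confidence is medium, since the materiality of any agent effect is undocumented.

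**What to change.** Add to section 2.4.2: follow-up scans use the agent given at the patient's baseline scan where supply and safety allow; otherwise the existing shortage rule applies. This stops changes from a substitute to regadenoson. It does not stop changes forced by a later shortage. For those, record the agent at every scan (if this is not already done) and report the primary incidence also in patients whose baseline and follow-up agents match. That report should be a sensitivity analysis, not a condition for the comparison with 17%.

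The cost is one sentence, one data field and one repeat analysis. Some patients will stay on a substitute after regadenoson is available again. Intervals in the matched subset are wider, as shown above, but with zero events the subset still excludes 17% provided it holds at least 20 patients. The primary analysis and the sample size do not change.

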### 2.5. Objectives

#### 2.5.1. Primary Endpoint

The primary outcome measure of this study is the occurrence of perfusion defects on cardiac SPECT scans during follow-up periods of 3, 6, and 12 months after radiation therapy.

#### 2.5.2. Secondary Endpoints

The secondary endpoints are as follows:-The incidence of left ventricular wall motion disorder and LVEF quantification on follow-up cardiac SPECT scans at 3-, 6-, and 12-months post-irradiation.-Measurement of the delivered doses to the cardiac volumes and their substructures.-The influence of cardiac risk factors on postradiation myocardial perfusion.-Assessment of the influence of chemotherapy/trastuzumab/trastuzumab emtansine exposure on postradiation myocardial perfusion.-Assessment of tumor-bed boost location on cardiac dose.

### 2.6. Participant Timeline

Figure 1 shows the different stages of the clinical trial.

### 2.7. Data Collection, Management, and Analysis

#### 2.7.1. Assessment of Myocardial Perfusion

A nuclear medicine physician (blinded to clinical information) will independently determine a visual score for each patient’s cardiac SPECT, aided by the quantification software (QGS/QPS Cedars-Sinai software), as performed in clinical practice. The 17-segment model cartography of the left ventricle recommended by the American Heart Association will be used for the evaluation of myocardial perfusion [41]. The relative perfusion to each segment will be quantified in five gradations of perfusion defect, with each assigned a numerical value as follows: 0 = no defect; 1 = mild defect/equivocal; 2 = moderate defect; 3 = severe defect; and 4 = absent perfusion. Normal studies, therefore, will have a summed stress score (SSS) or summed rest score (SRS) of 0 and the highest possible score of 68 (absent perfusion in all 17 segments).

